### Participant timeline {13}

The participant timeline consists of three phases:Pre-hospital phase: The timeline starts before the hospital stay with an interaction between a potential participant and a referring entity (e.g. a GP), during which the need for hospitalisation is assessed. If the referring entity determines that the potential participant meets the eligibility criteria for the intervention, the STATAMED ward is contacted for the mandatory case review between the referring physician and the lead STATAMED physician. If the eligibility criteria are met, the admission is scheduled to take place approximately 1–2 days later.Hospital phase: Upon provision of informed consent and admission to the STATAMED ward, participants are formally enrolled in the study. The hospital stay is expected to last approximately 3 days on average. During this period, patients receive standard general medical treatment in the STATAMED unit, and case managers assist with interdisciplinary care planning and discharge preparations.Posthospital phase (up to 28 days after discharge): After discharge, follow-up care is available. The mobile nurse may visit the patient at home or in a care facility. Case managers can assist patients during the hospital stay and after discharge, coordinating follow-up care and addressing post-discharge needs.

Figure 3 illustrates the participant timeline, covering the pre-hospital, hospital, and posthospital phases.

All assessments of primary and secondary outcomes will be conducted using claims data from statutory health insurers. Data collection does not require any direct involvement from participants.

**Fig. 3 Fig3:**
[figure not shown]
Participant timeline. Notes: *The case review takes place between the referring entity and the lead STATAMED physician

### Sample size {14}

The required sample size was estimated prior to project implementation using Bonferroni correction to account for multiple comparisons because the trial includes two co-primary outcomes without a hierarchical structure: (1) length of hospital stay and (2) 30-day hospital readmission. Applying a type 1 error rate of *α* = 5%, the Bonferroni correction results in a per-outcome significance level of α/2 = 2.5% for confirmatory testing.

Sample size calculations were performed according to Woertman et al. [38]. Based on existing literature [39] and a pre-analysis of claims data, a minimum relevant difference of 15% was specified for both co-primary outcomes. An intra-class correlation coefficient (ICC) of *ρ* = 0.05 was assumed to account for within-cluster correlation [40, 41], resulting in a design effect estimate of 0.61.

For co-primary outcome (1), the required sample size was estimated at 2331 participants; this increases to 2681 participants after adjusting for a 20% drop-out rate. For co-primary outcome (2), the required sample size was estimated at 3724 participants, rising to 4481 after applying the same drop-out assumption. Given that both outcomes are co-primary, the larger of the two estimates (i.e. 4481 participants) was initially adopted as the required sample size for the intervention group across all clusters over the full duration of the study.

These initial calculations relied on conservative assumptions, including a high estimated drop-out rate and the use of the Bonferroni correction for multiple comparisons. However, evidence from the literature and ongoing implementation experience allow for the following refinement of these assumptions.

Based on recent experience with implementation logistics and recruitment patterns, a more realistic drop-out rate of 15% is now assumed. In addition, Leppin et al. [42] conducted a meta-analysis that found an 18% reduction in the risk of readmission. Complex interventions and interventions ensuring structured follow-up care are found to be particularly effective in reducing readmission. Because both elements are core features of STATAMED, an effect size of 20% is considered plausible.

Finally, to adjust for multiple comparisons, the Romano-Wolf method [43] offers an alternative to the Bonferroni correction. This method controls the family-wise error rate using a step-down bootstrap procedure that accounts for the correlation among hypotheses, thereby making more efficient use of the global *α* level. Applying this method permits the use of a global significance level of 5% for sample size calculation.

Under these updated assumptions (i.e. 20% effect size, 15% drop-out rate and Romano-Wolf correction), the required sample size is reduced to 2076 participants for the readmission outcomes and 578 for length of stay. Accordingly, 2076 participants are required for evaluating the combined primary outcome.

The sample size calculation refers to the required number of participants for whom claims data are available. This is important because claims data are only available for patients insured by one of the participating statutory health insurers.

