## Trial design {8}

The STATAMED study will be conducted as a prospective, cluster-randomised controlled trial (C-RCT) using a stepped-wedge design at six hospital sites. The catchment areas of the participating sites will be divided into clusters based on postal codes. Clusters were formed using the number of referring entities (e.g. GPs, specialists, nursing homes, ambulatory care services, and emergency services) as the criterion, with the goal of creating a sufficient number of clusters of approximately equal size to facilitate analysis and ensure sufficient statistical power [34].

The stepped-wedge design entails each cluster beginning in a control phase and sequentially transitioning to the intervention phase in staggered steps. Each cluster undergoes a 3-month transition phase to practice and refine the intervention before fully entering the intervention phase. The shift from the control phase to the transition phase is divided into four steps, with one-quarter of the clusters transitioning every 3 months. This staggered approach allows intervention effects to be recorded and compared over time [35]. Once a cluster transitions into the intervention phase, it will remain in this phase for the duration of the study. After the intervention phase, a follow-up phase will be conducted to complete all outcome measurements. Figure 1 illustrates the study design.

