### Concealment mechanism {16b}

This is not applicable. Patients who meet the eligibility criteria and whose referring entity is located in a cluster assigned to the transition or intervention phase can participate in STATAMED. Before admission to a STATAMED ward, patients must provide informed consent to participate in the project.

The control groups will consist of patients who meet the eligibility criteria but receive treatment at a non-STATAMENT hospital. They will be identified retrospectively based on ICD-10 codes available in the claims data from the participating health insurers.

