### Implementation {16c}

The allocation sequence will be generated through randomisation (see “Sequence generation {16a}”). The randomisation process will be conducted by the authors.

Participants will be enrolled at their respective STATAMED wards. Assignment to the intervention will depend on the cluster to which the referring entity is assigned. Patients who meet the eligibility criteria and whose referring entity is in a cluster currently in the intervention phase will be able to participate in STATAMED.

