### Trial status

Recruitment started in April 2024. The current protocol is version 1, dated 17 July 2025. Recruitment is expected to continue until March 2026.

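### The design effect of 0.61 fits a stepped wedge without a transition phase; it should be recomputed for the layout the protocol describes, and the power for 2076 restated

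*Protocol article*

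**What the plan says.** Protocol article, Sample size {14}: "An intra-class correlation coefficient (ICC) of *ρ* = 0.05 was assumed", "resulting in a design effect estimate of 0.61". The section cites a published stepped-wedge method. It first requires 3724 participants for readmission (4481 with drop-out), counted in the intervention group over the whole study. It then lowers the requirement to 2076 using a 20% effect, 15% drop-out and a 5% significance level. It mentions no transition phase.

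Trial design {8}: "Each cluster undergoes a 3-month transition phase to practice and refine the intervention before fully entering the intervention phase". There are four steps, "with one-quarter of the clusters transitioning every 3 months", and every cluster begins in a control phase.

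Sequence generation {16a}: one randomly chosen cluster per site starts at the beginning of the study, and each ward adds at most one cluster per step. Trial status: recruitment began in April 2024; "Recruitment is expected to continue until March 2026".

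The entry rule is given in two forms. Concealment mechanism {16b} says that eligible patients whose referring entity is "located in a cluster assigned to the transition or intervention phase can participate in STATAMED". Implementation {16c} speaks only of those "whose referring entity is in a cluster currently in the intervention phase will be able to participate in STATAMED". Trial design {8} counts all eligible patients treated in a STATAMED ward as the intervention group.

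**The concern.** A design effect belongs to a particular layout. A stepped wedge draws much of its information from the cluster-periods either side of the switch, and the transition phase removes one of them in every cluster. Intervention quarters with no cluster left in the control phase add little to the effect estimate once calendar time is modelled, as Statistical methods {20a} rightly requires. If 0.61 describes a layout with neither feature, 2076 is tied to a precision that the trial may not reach on its randomised comparison. The unsettled status of transition-phase patients adds to this: people treated while the ward is still practising could be counted towards 2076.

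**Working it through.** **1. Reproducing 0.61.** With k steps, b baseline periods, t measurements per step, n patients per cluster-period and ICC ρ:

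DE = [1 + ρ(ktn + bn − 1)] / [1 + ρ(ktn/2 + bn − 1)] × 3(1 − ρ) / [2t(k − 1/k)]

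From the protocol: k = 4, ρ = 0.05. Assumed: b = 1, t = 1, n = 62.

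DE = (1 + 0.05 × 309) / (1 + 0.05 × 185) × 2.85 / 7.5 = (16.45 / 10.25) × 0.38 = 0.6099.

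The formula has no transition term. Generalised least squares on the same layout (random cluster effect, fixed period effects) gives the same 0.6099 per measurement period, so the result does not depend on the cited source. The protocol does not state n. With b = 1, any n from 51 to 81 rounds to 0.61; b = 0 with n = 14-15 does too. The choice n = 62 fits the protocol's own count: 24 clusters in four steps have 6 × (4 + 3 + 2 + 1) = 60 intervention cluster-periods, and 60 × 62 = 3720, against 3724.

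**2. Is 0.61 carried into 2076?** Scale 3724 by the stated changes (effect 15% to 20%, two-sided significance level 2.5% to 5%), then divide by 0.85:

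- 80% power: 3724 × (0.15/0.20)² × [(1.960 + 0.842)/(2.241 + 0.842)]² / 0.85 ≈ 2035
- 90% power: ≈ 2086

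Both lie within 3% of 2076, so no new design effect appears to have been used.

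**3. The described layout.** There are 24 months, or 8 quarters. Figure 1 is not shown, so two starts are considered:

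- *First step at month 0:* 6 control, 4 transition and 22 intervention wave-quarters. The last wave leaves control after 9 months, so 15 of 24 months have no control-phase cluster. Only 3 of 22 intervention wave-quarters have concurrent controls.
- *One baseline quarter first:* 10 control, 4 transition and 18 intervention wave-quarters. The last wave leaves control after 12 months. Only 3 of 18 intervention wave-quarters have concurrent controls.

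A third layout isolates the transition gap: one baseline quarter and 6 quarters in all, with 10 control, 4 transition and 10 intervention wave-quarters.

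**4. Variance and power.** Assumptions: 24 clusters (6 sites × 4 steps), ICC 0.05, 2076 × 0.85 = 1765 analysed intervention patients spread evenly, transition excluded, control group 1 only, a free effect for each quarter, two-sided 5%, nominal power 80%. R is the variance relative to the no-transition layout with the same 1765 patients and equal cells. Power = Φ[(1.960 + 0.842)/√R − 1.960].

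| Layout | R, equal cells | Power | R, control cells 10× | Power |
|---|---|---|---|---|
| Transition gap alone | 1.76 | 56% | 0.74 | 90% |
| Gap, 24 months, one baseline quarter | 2.77 | 39% | 1.30 | 69% |
| Gap, 24 months, first step at month 0 | 3.36 | 33% | 1.82 | 55% |

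Example: 2.802/√3.36 − 1.960 = −0.43, and Φ(−0.43) = 0.33. For ICC 0.01 to 0.10 the equal-cell ratios stay at 1.76-1.80, 2.73-2.96 and 3.33-3.56.

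**The case against.** The strongest reply is that the protocol does not contain enough to show a shortfall. It states no power, number of clusters, cell size or control count. Figure 1 is not shown, and a first step at month 0 sits badly with the statement that every cluster begins in a control phase. Controls come from claims data without consent, so 2076 does not limit them and equal cells are an unfavourable case. The form of the time adjustment may properly be left to an analysis plan. With a linear trend plus season instead of free quarter effects, and the first step at month 0, power is 52% with equal cells and 72% with 10-fold controls; with four pre-trial quarters and 3-fold controls it is 85%. Counting transition patients as intervention gives 49-55% with equal cells and 75-87% with 10-fold controls on the 24-month layouts. Adding 24 never-treated control group 3 clusters at equal cell size gives 86-93%. The Figure 2 legend also marks the transition phase separately from the intervention and control groups.

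All of this stands as a limit on the size of the loss. A reader might infer that 2076 certainly fails to deliver its power; the protocol does not support that, because the result depends on choices it does not state. A reader might also infer that 0.61 was multiplied directly onto total patients. It is a per-period factor: over 5 periods with new patients in each, the factor on total patients is 0.61 × 5 ≈ 3.05. But the unadjusted sample size is not given, so direct use cannot be confirmed, and the 3720 match points the other way.

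The reply does not rescue 0.61 itself, which describes a layout other than the one in Trial design {8}. Nor does it settle the difference between {16b} and {16c}.

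**Conclusion.** The point holds in a conditional form. The figure 0.61 is reproduced for a stepped wedge without a transition phase and appears to carry through to 2076, while the trial has a 3-month transition in every cluster and a long period with no control-phase cluster. Under the assumptions in the working, the variance is about 1.8 times (gap alone) to 3.4 times (24 months, first step at month 0) that of the layout behind 0.61, and a nominal 80% becomes about 33-56%. Control cells 10 times larger restore the power for the gap alone, but the two 24-month layouts stay at about 55-69% with control group 1 only and free quarter effects. The 80% is an assumption, not a protocol figure. The conflict over entry in the transition phase rests on the text alone.

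**What to change.** 1. Recompute the design effect from the actual quarter-by-quarter layout, including the transition quarters and the quarters without control-phase clusters. State the number of clusters, cluster-period sizes and expected claims-based control numbers. Restate the power or the detectable effect for 2076; this does not require enrolling more patients.
2. Reconcile Trial design {8}, Concealment mechanism {16b} and Implementation {16c} on whether transition-phase patients may enter and count. For the analysis, leave transition cluster-quarters out of the main effect estimate and do not count them towards 2076.
3. A model that adds control group 3 areas as never-treated clusters may be offered as a sensitivity analysis, stating its assumption of a common calendar trend inside and outside the catchment areas. Keep the randomised stepped-wedge comparison as primary; moving non-randomised areas into it would be a trade-off, not a correction.

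The cost is a recalculation and some rewording. The downside is that the stated power or detectable effect becomes less favourable.

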**Methods:**

The study will be conducted as a prospective, cluster-randomised controlled trial using a stepped-wedge design. STATAMED wards will be implemented at six hospital sites, and the catchment areas will be divided into clusters. All referring entities in a catchment area—including general practitioners (GPs), office-based specialists, nursing homes, ambulatory care services, and emergency services—will be potential candidates for cluster formation. The intervention group is expected to consist of 4481 patients. Primary and secondary outcomes will be assessed using claims data from participating statutory health insurers. A health economic evaluation will also be conducted using these data to compare costs associated with STATAMED and usual care. To minimise the risk of bias, analyses will be conducted on both an intention-to-treat and actual treatment basis.

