### Statistical methods

#### Statistical methods for primary and secondary outcomes {20a}

The two co-primary outcomes (length of hospital stay, 30-day hospital readmission rate) are treated as continuous variables. The secondary outcomes (utilisation of hospital emergency departments, emergency outpatient care, and nonemergency outpatient care, as well as place of discharge) are also continuous except for the place of discharge (home, care facility, other), which is categorial.

Because there are two co-primary outcomes without hierarchical ordering, a correction for multiple testing is required. A Bonferroni correction will be applied, resulting in a one-sided significance level of α/2 = 2.5% for each primary outcome given a global type I error rate of *α* = 5%. However, the Bonferroni method is known to be conservative. As an alternative, the Romano-Wolf procedure [43] may be used, as it more efficiently controls the family-wise error rate by accounting for the dependence structure among outcomes through resampling (see “Sample size {14}”).

When analysing stepped-wedge designs, it is important to account for temporal effects given that each cluster transitions to the intervention in a stepwise fashion. In this study, this is particularly important because the STATAMED wards will gain experience with implementing the intervention over time. Additionally, the longitudinal design of the study necessitates the consideration of calendar time because patient case mix may vary by season (e.g. winter versus summer) due to the focus of the study on general medical conditions. To account for these temporal effects, generalised linear mixed models (GLMMs) and generalised estimating equations (GEEs) will be applied [45–47]. Propensity score matching, considering age, gender, and morbidity, will be used to ensure comparability between the control and intervention groups.

To avoid bias from patients who are transferred to other hospitals during STATAMED treatment or those who meet eligibility criteria but prefer to be treated at a non-STATAMED hospital, the analysis will be conducted according to the intention-to-treat and per-protocol principles [48].

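### Two length-of-stay sample sizes (2681 and 578) do not follow from the stated inputs, and the abstract still gives the superseded target of 4481; the operative target of 2076 is not affected

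*Protocol article*

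**What the plan says.** All the figures are in the protocol article, section Sample size {14}, unless another place is named.

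- Initial assumptions: "a minimum relevant difference of 15% was specified for both co-primary outcomes", and "the Bonferroni correction results in a per-outcome significance level of α/2 = 2.5% for confirmatory testing". An ICC of 0.05 is assumed, "resulting in a design effect estimate of 0.61".
- Initial length of stay: "the required sample size was estimated at 2331 participants; this increases to 2681 participants after adjusting for a 20% drop-out rate".
- Initial readmission: "the required sample size was estimated at 3724 participants, rising to 4481 after applying the same drop-out assumption". The larger figure, 4481, was first adopted as the size of the intervention group.
- Update: the section then assumes 15% drop-out, a 20% effect and a 5% significance level (through the Romano-Wolf procedure). On that basis "the required sample size is reduced to 2076 participants for the readmission outcomes and 578 for length of stay", and 2076 is named as the number required for the combined primary outcome.
- Abstract, Methods: "The intervention group is expected to consist of 4481 patients".

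Power, SD and baseline readmission rate are not given. Sidedness appears only in Statistical methods for primary and secondary outcomes {20a}: "resulting in a one-sided significance level of α/2 = 2.5% for each primary outcome".

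**The concern.** Three things do not fit together.

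1. One 20% drop-out rate produces two different uplifts, and the one for length of stay is exactly what 15% would give.
2. The update changes the same three assumptions for both outcomes. Both requirements should therefore shrink by nearly the same factor. Readmission falls to 46% of its initial value and length of stay to 22%.
3. The abstract and the sample size section give different sizes for the same group.

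These are the published requirements for the two co-primary outcomes. They support more than halving the target while recruitment is under way. A reader who tries to retrace them cannot do so for length of stay, and one who reads only the abstract takes away a target that the article itself has replaced.

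**Working it through.** **Drop-out, initial figures.** Inputs: 2331 to 2681 and 3724 to 4481, both said to reflect 20%. The two common conventions are N x (1 + d) and N/(1 - d).

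| Outcome | N before | N stated | Factor | N x 1.2 | N/0.80 | Left after 20% loss |
|---|---|---|---|---|---|---|
| Length of stay | 2331 | 2681 | 1.150 | 2797 | 2914 | 2681 x 0.8 = 2145 |
| Readmission | 3724 | 4481 | 1.203 | 4469 | 4655 | 4481 x 0.8 = 3585 |

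The plan's 2681 is reproduced by 2331 x 1.15 = 2681, not by either form of 20%. The plan's 4481 is within 0.3% of 3724 x 1.2. Neither total fully covers a 20% loss: 2145 is below 2331 and 3585 is below 3724. The loss that each can absorb is 1 - 2331/2681 = 13.1% and 1 - 3724/4481 = 16.9%. This step needs no assumption about power or variance.

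**Updated figures.** For a fixed design, N is proportional to (z_alpha + z_power)^2 / effect^2. SD, baseline rate and a constant design effect cancel, so

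N_new = N_old x (0.15/0.20)^2 x [(z at alpha 5% + z_power)/(z at alpha 2.5% + z_power)]^2,

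and the result is then inflated for 15% drop-out.

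At 80% power, two-sided: 0.5625 x [(1.960 + 0.842)/(2.241 + 0.842)]^2 = 0.5625 x 0.8258 = 0.4645.

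- Readmission, as a check on the method: 3724 x 0.4645 = 1730; 1730/0.85 = 2035. Stated: 2076.
- Length of stay: 2331 x 0.4645 = 1083; 1083/0.85 = 1274. Stated: 578.

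Power is not stated and the sample size section gives no sidedness, so both were varied. The first number in each cell is N/0.85, the second N x 1.15.

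| Sides, power | Length of stay (stated 578) | Readmission (stated 2076) |
|---|---|---|
| Two-sided, 70% | 1245; 1217 | 1988; 1944 |
| Two-sided, 80% | 1274; 1245 | 2035; 1989 |
| Two-sided, 90% | 1306; 1277 | 2086; 2039 |
| Two-sided, 95% | 1327; 1297 | 2120; 2073 |
| One-sided, 70% | 1176; 1150 | 1879; 1837 |
| One-sided, 80% | 1215; 1188 | 1941; 1898 |
| One-sided, 90% | 1257; 1229 | 2009; 1963 |
| One-sided, 95% | 1285; 1256 | 2052; 2006 |

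Length of stay ranges from 1150 to 1327, and 578 is 44% to 50% of that. Readmission ranges from 1837 to 2120, which contains 2076.

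**Could another input explain 578?**

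- Two-sided in the first calculation and one-sided in the second gives 928 to 1105 for length of stay. It also breaks the match for readmission (1482 to 1766).
- A smaller design effect is not enough. With the standard stepped-wedge formula, four steps, and one baseline and one measurement per step (assumed), it falls from 0.61 to about 0.41 even at one patient per cluster-period. Applied to 1274 this gives 1274 x 0.41/0.61 = 856.
- At 80% power, 578 would need an effect of about 29% to 30%, against the stated 20%.

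**Does it matter for the operative target?** With 2076 enrolled and 15% lost, 2076 x 0.85 = 1765 remain. If the original calculation used 80% power, two-sided, then for length of stay z = 3.083 x sqrt(1765/2331) x 20/15 = 3.58. Power at 5% is then Phi(3.58 - 1.96), about 95%. For readmission z = 3.083 x sqrt(1765/3724) x 20/15 = 2.83, and power is about 81%.

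**The case against.** The strongest reply is that nothing operative depends on the disputed numbers. The requirement is 2076, it is set by readmission, and it roughly reproduces. 2681 was never the target, 4481 has been superseded, and 578 does not bind. This stands, and it limits the point to a correction of the text.

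Multiplying by 1 + d is a common, if less exact, convention, so the shortfall of 4481 against a 20% loss is mainly a matter of convention. This also stands. What remains is that the two outcomes carry different uplifts for one stated rate.

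A misprint is possible: 2234 x 1.2 = 2681 and 3734 x 1.2 = 4481. It cannot be confirmed or excluded from the article, so 2914 and 4655 are right only if 2331 and 3724 are.

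A reader might infer two stronger things.

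- That the reduction was applied twice, since 2681 x 0.4645^2 = 578. The match holds at two-sided 80% power, but the same idea gives 526 one-sided at 80% and 608 two-sided at 90%. Power is unstated and the only stated sidedness is one-sided, so the documents do not support this explanation.
- That length of stay would have only about 47% power, which is what 578 patients less 15% give for a 20% effect at two-sided 5%, taking 80% power as the starting point. No one plans to stop at 578, so this is not a consequence for the trial.

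**Conclusion.** The point holds as an error in the stated figures. The step from 2331 to 2681 contradicts its own 20%, whatever the power or variance. The figure of 578 cannot be reached from the three stated changes: they give about 1150 to 1330, so 578 is roughly half or less of what the inputs imply. That second conclusion assumes that SD, power and design effect stayed the same, since no change in them is stated. The abstract's 4481 is out of date against the article's own 2076.

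The documents do not support a claim that the trial is undersized for length of stay. At 2076 that outcome has about 95% power under the 80%, two-sided assumption. The point is moderate: published figures need correcting, and enrolment does not change.

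**What to change.** 1. Recheck the source calculation, including whether 2331 and 3724 are printed correctly.
2. Reconcile 2331/2681 and 3724/4481 with a 20% drop-out by one formula, preferably N/(1 - d). If the pre-drop-out figures are right, this gives 2914 and 4655.
3. Correct 578 to the value that the source calculation gives (roughly 1150 to 1330, depending on the power and sidedness used), or state the additional changed input that produces it.
4. Give 2076 as the single current target in the abstract, and mention 4481 only as the initial figure.

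The cost is a text correction. No additional patients are needed and the analysis does not change.

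### The reduced target of 2076 is derived with Romano-Wolf at an unsplit 5%, but the analysis commits to Bonferroni at one-sided 2.5% per outcome; sizing and confirmatory test need one procedure and one sidedness

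*Protocol article*

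**What the plan says.** The Sample size section of the protocol article starts from Bonferroni: "the Bonferroni correction results in a per-outcome significance level of α/2 = 2.5% for confirmatory testing". On effect size, "a minimum relevant difference of 15% was specified for both co-primary outcomes". With 20% drop-out this gives 3724 participants for readmission, raised to 4481.

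The same section then revises three assumptions: drop-out falls to 15%, the effect rises to 20%, and Bonferroni gives way to Romano-Wolf. On the last it says: "Applying this method permits the use of a global significance level of 5% for sample size calculation". The result is 2076 for readmission and 578 for length of stay, and 2076 becomes the requirement.

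The section on statistical methods for primary and secondary outcomes says: "A Bonferroni correction will be applied, resulting in a one-sided significance level of α/2 = 2.5% for each primary outcome". Of the other method it says only: "As an alternative, the Romano-Wolf procedure [43] may be used".

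The article gives no power, baseline readmission rate or standard deviation for the sizing. It calls the test level one-sided in the methods section and gives no sidedness in the sample size section.

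**The concern.** The multiplicity method is one of three named reasons for more than halving the target, yet it is not the method the analysis commits to. This is not detail left to a later analysis plan: the article fixes both sides, and they disagree.

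The reason given for using 5% is also incomplete. Romano-Wolf holds the family-wise error at 5% across both outcomes. It does not test readmission at 5% from the start; that level is reached only once length of stay has been rejected.

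Two things are at stake. The first is the power that 2076 gives for readmission. The second is the decision rule: a readmission p-value between 0.025 and 0.05 fails under Bonferroni but succeeds under a step-down test in which length of stay has been rejected.

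**Working it through.** **Inputs from the Sample size section.** Readmission: 3724 before drop-out, for a 15% effect at 2.5%. Length of stay: 2331 on the same basis. Revised: 20% effect, 15% drop-out, total 2076. **Assumed, because not stated:** power of 80% or 90%; one- or two-sided levels; a normal approximation in which the required N varies with the inverse square of the effect; drop-out applied as N × 1.15 or N / 0.85.

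**Step 1. Which level does 2076 embody?** It cannot be rebuilt from first principles, so I scale 3724:

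N = 3724 × (15/20)² × [(z_new + z_power) / (z_2.5% + z_power)]²

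- At 2.5% the bracket is 1. N = 3724 × 0.5625 = 2095, which is 2409 (× 1.15) or 2464 (/ 0.85) with drop-out.
- At an unsplit 5%, with drop-out:

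| Sizing | × 1.15 | / 0.85 |
|---|---|---|
| One-sided, 80% | 1898 | 1941 |
| One-sided, 90% | 1963 | 2009 |
| Two-sided, 80% | 1989 | 2035 |
| Two-sided, 90% | 2039 | 2086 |

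The stated 2076 fits an unsplit 5%, best with two-sided levels, and does not fit 2.5%. A two-proportion version of the scaling leads to the same conclusion.

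**Step 2. Readmission power at 2076, equal sidedness.** Analysed: 2076 × 0.85 = 1765. The expected test statistic for a 20% effect is

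δ = (z_2.5% + z_power) × √(1765/3724) × 20/15

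Two-sided, 80% base: δ = (2.241 + 0.842) × 0.688 × 1.333 = 2.83. Power at 5% = Φ(2.83 − 1.960) = 0.81; at 2.5% = Φ(2.83 − 2.241) = 0.72.

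| Base | Power at 5% | Power at 2.5% |
|---|---|---|
| Two-sided, 80% | 81% | 72% |
| One-sided, 80% | 82% | 73% |
| Two-sided, 90% | 90% | 84% |
| One-sided, 90% | 91% | 85% (0.845) |

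For smaller effects, two-sided at 2.5%: 62% (18% effect) and 45% (15%) on the 80% base; 75% and 57% on the 90% base.

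**Step 3. Mixed sidedness.** A two-sided 5% test and a one-sided 2.5% test in the direction of benefit share the critical value 1.960. If the sizing used the first and the analysis uses the second, power for a 20% effect stays at 81% (80% base) or 90% (90% base).

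**Step 4. What Romano-Wolf gives.** For two outcomes, the first-step level solves P(largest statistic exceeds c) = 5% under a bivariate normal. At correlation 0 it is 1 − √0.95 = 2.53%. At 0.5 it is 2.70% two-sided or 2.77% one-sided. The level rises to 5% for readmission only after length of stay is rejected.

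**Step 5. Step-down power for readmission** (two-sided, 80% base, 20% effect on both outcomes, first step at 2.5%, tests treated as independent). For length of stay, δ = 3.083 × √(1765/2331) × 20/15 = 3.58, so power at 2.5% = Φ(3.58 − 2.241) = 0.909. For readmission: 0.909 × 0.808 + 0.091 × 0.722 = 0.80, against 0.81 at an unsplit 5%.

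**The case against.** The strongest reply is that no power need be lost. Step 1 fits best with two-sided levels, the methods section tests one-sided, and that pairing shares one critical value. This stands as a possibility, and it rules out the flat conclusion, which a reader might draw, that 2076 is too few. It does not remove the mismatch. Both sections use the same 5% and half of it, only one attaches a side, and the Sample size section attributes the change to the multiplicity method, not to sidedness. If mixed sidedness is the explanation, the text must say so.

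Second, sizing on Romano-Wolf costs little if length of stay really falls by 20%. That also stands: about one point in Step 5. The article's own 578 for length of stay would imply even less, since at 2076 its power at 2.5% would exceed 99%. However, 578 does not scale from 2331 (roughly 1190-1310 would be expected), so I do not rely on it. The 72% figure is Bonferroni power at equal sidedness, and roughly what Romano-Wolf's first step gives, not step-down power under the planned effects.

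Three stronger readings are tempting but unsupported:

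- *Both outcomes would be tested at 5%, with a family-wise error near 9.75% (1 − 0.95²) if independent.* The article speaks of a global level and of family-wise control, and proposes no such analysis.
- *The choice of method is deferred until results are known.* The article sets no time for it, and an analysis plan not shown may fix it before the data deliveries of about June 2026 and January 2027.
- *The 20% effect is itself a contradiction.* It exceeds the 15% minimum relevant difference and the cited meta-analysis, which "found an 18% reduction in the risk of readmission". But the article discloses all three figures and gives a reason why "an effect size of 20% is considered plausible". This is debatable and separate from multiplicity; it matters here only as a reason to report power at 18% and 15% too.

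**Conclusion.** The inconsistency is certain from the text: 2076 assumes Romano-Wolf, while the committed test is Bonferroni. That 2076 embodies an unsplit 5% for readmission is an inference from scaling the plan's own 3724, and no variant at 2.5% comes close.

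The effect on power is conditional. At equal sidedness, and for a 20% effect, Bonferroni costs readmission about 9 points on an 80% base and about 6 on a 90% base; about 2410-2460 participants would then match. With two-sided sizing and a one-sided test it costs nothing. Under step-down testing with length of stay also cut by 20%, it costs about one point. The documents do not say which case applies, so none of these percentages is a property of 2076 until the sponsor states power and sidedness.

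**What to change.** In the statistical methods section, replace the Bonferroni commitment and the optional alternative with one committed step-down procedure, Romano-Wolf or Holm, at a global 5%. State one sidedness and use it in both the sample size and statistical methods sections.

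In the Sample size section, add that 5% applies to readmission only once length of stay has been rejected. Then restate, from the sponsor's own power and baseline inputs, what 2076 delivers under that procedure for effects of 20%, 18% and 15%. The assumed percentages above should not be copied in. If Bonferroni is kept instead, restate the power at 2.5%.

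The cost is wording and a recalculation, with no additional enrolment. At equal sidedness, step-down is never less powerful than Bonferroni. If two-sided testing replaces the present one-sided 2.5%, the text should say that the first-step threshold becomes stricter (2.241 against 1.960 with Holm). The stated power may become less favourable. The change is best made before the preliminary data delivery.
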